| 2.0            | 30Nov18             | Clarify the timelines for data collection.
Change in information recorded on deliveries.
Update the CRFs accordingly                                                                                                               |
| 2.1            | 26 June 2019        | Correction of one of the two satellite sites in Spain                                                                                                                                                                                    |
| 3.0            | 1 Nov2019           | Collection of 4 additional data points to obtain reliable count of outcomes of interest
Simplify the recruitment rules of study participants
Update information on participating sites, scientific committee members and timelines |

## Acronyms

|       |                                                                 |
|-------|-----------------------------------------------------------------|
| AEFI  | Adverse Event Following Immunization                            |
| CI    | Confidence interval                                             |
| CRF   | Case report form                                                |
| CIOMS | Council for International Organizations of Medical Sciences     |
| DMP   | Data management plan                                            |
| eCRF  | Electronic case report form                                     |
| EDC   | Electronic data capture                                         |
| GAIA  | Global Alignment of Immunization Safety Assessment in Pregnancy |
| GACVS | Global Advisory Committee on Vaccine safety                     |
| GDPR  | General Data Protection Regulation                              |
| HICs  | High income countries                                           |
| ICD   | International Classification of Diseases                        |
| LMICs | Low and middle-income countries                                 |
| LMP   | Last menstrual period                                           |
| PPV   | Positive predictive value                                       |
| RSV   | Respiratory Syncytial Virus                                     |
| USA   | United States of America                                        |
| WHO   | World Health Organization                                       |

## Roles and responsibilities

|                                                                        |
|------------------------------------------------------------------------|
| Scientific committee                                            |
| Provide scientific guidance in protocol development and implementation |
| Review study data analysis and study results                           |
| WHO (Headquarters)                                              |
| Oversight and coordination                                             |
| Site selection                                                         |
| Ethics and other approval at WHO level                                 |
| Country coordinators/managers                                   |
| Primary contact point between sites in a country and WHO               |
| P95/INCLIN                                                      |
| Development of EDC system and pilot testing                            |
| Country-level training                                                 |
| Data management plan and statistical analysis plan                     |
| Coordinates receipt of data from all sites                             |
| For-cause site monitoring                                              |
| Data cleaning, including sending site-specific queries                 |
| Data analysis                                                          |
| Reporting                                                              |

|                                          |
|------------------------------------------|
| Study Sites                       |
| Ethics and other approval at local level |
| Pilot testing of EDC at selected sites   |
| Obtaining informed consent               |
| Case identification                      |
| Completion of eCRFs                      |
| Answering site-specific queries          |

## 2 Background

Immunological and physiological changes during pregnancy may increase a woman's risk of infection. The relative immunological inexperience of the foetus and neonate poses additional risk of infection for the developing infants as well [1]. Through 2015, neonatal death accounted for approximately 46% of mortality among children less than 5 years of age globally and of these deaths, 25% were caused by infection [2].

Immunization during pregnancy can protect the pregnant woman and her child, both in the womb and in early life. The goal of immunizing women during pregnancy is to increase their antibody titres against certain vaccine-preventable diseases, so that high and protective levels of antibody are transferred to the infant during the pregnancy. Hence it can prevent infectious diseases in infants who are too young to benefit directly from primary immunization and protect the foetus from the effects of maternal infection during development.

Many diseases have a disproportionate impact on the young infant. These include pertussis, influenza, group B streptococcal (GBS) infection, respiratory syncytial virus (RSV) and tetanus. For tetanus, pertussis and influenza, immunization in pregnancy is a key strategy to prevent significant morbidity and mortality amongst young infants globally and it also holds great promise as a strategy to protect infants from other infections [3-5]. The ultimate goal of immunization in pregnancy is to decrease morbidity and mortality among pregnant women, neonates and infants. This public health strategy is of specific interest for low and middle-income countries (LMICs), where access to basic health services may be limited and the burden of vaccine-preventable diseases is largest. Promising new vaccine products are being developed for use during pregnancy to protect unborn children and neonates from infection, such as vaccines against Zika, RSV, group B streptococci and hepatitis E vaccines. [6]

The risk-benefit ratio of vaccines in pregnancy must be assessed by balancing vaccine safety with the risk of infection for the pregnant woman and her foetus or infant in the absence of immunization [1]. Vaccine safety can only be inferred from low rates of adverse events following immunization (AEFI) that have been assessed in a relatively large population, and cannot be evaluated directly [7]. Vaccine safety surveillance is complex, and even more so during pregnancy, where the risk of adverse outcomes may change as a result of exposure to infection or vaccination over the gestational period [1]. In LMICs, safety monitoring is further challenged by the general lack of pharmacovigilance infrastructure [8].

The World Health Organization (WHO) Global Advisory Committee on Vaccine safety (GACVS) has evaluated the data on the safety of immunization of pregnant women for several inactivated and live attenuated vaccines. It concluded that there is no evidence of adverse pregnancy outcomes from the vaccination of pregnant women with inactivated virus, bacterial vaccine, or toxoid [1].

Post-marketing safety surveillance of new vaccines used during pregnancy is important for the detection of any AEFI in pregnant women and their infants for a number of reasons. First, background rates for the various outcomes of interest are not available in most LMICs; second, large populations are required to identify potential rare AEFI [7]. In addition, post-marketing safety surveillance may help to overcome existing barriers to vaccination during pregnancy as they will inform on the supposed risks to the foetus [1].

In response to the call of WHO for a globally concerted approach to monitor the safety of vaccine in pregnancy, the Global Alignment of Immunization Safety Assessment in Pregnancy (GAIA) project was launched in 2015. The aim of GAIA, managed by the Brighton Collaboration [9], was to improve generated data to facilitate data comparability and interpretation across surveillance systems, ultimately leading to strengthened programs of immunization in pregnancy [10, 11]. To this end, standardized definitions for obstetric and neonatal health outcomes were developed. The purpose of this harmonization and standardization is to increase the ability to conduct meaningful comparisons of safety data across studies [7, 9]. Within each case definition, multiple 'Levels of diagnostic certainty' are recognized, so that the definitions are globally applicable for all immunization safety purposes and in settings with different levels of diagnostic capacities [9].

As several promising vaccines in development would be of great benefit specifically for women and children in low and middle-income countries (LMICs), due to higher perinatal and infant mortality rates, it is now critical that those countries develop vaccine safety monitoring beyond passive surveillance, in this specific population.

In an effort to address WHO's Global Vaccine Safety Blueprint (5) strategic goal of enhanced pharmacovigilance capacity, the Global Vaccine Safety Initiative (6), through its WHO secretariat, tested the development of a global network of hospital-based sentinel sites of LMICs across the WHO regions for vaccine safety signal verification and hypothesis testing. The aim of the project was to identify optimal models and processes for establishment and operationalization of such a network. The lessons learnt from this proof of concept project will be integrated in the development of this study [12].

## 2.1 Rationale

The goal of this prospective study is to estimate the minimum detectable risk for selected neonatal outcomes (neonatal death, neonatal infection, congenital microcephaly, low birth weight, preterm birth, small for gestational age, and stillbirth) in each study site using standardised case definitions and to assess the applicability of GAIA case definitions in LMICs, in order to inform future vaccine safety studies.

The use of GAIA case definitions can be challenging in LMICs, as the proposed criteria for some definitions can exceed the clinical capacity of some sites. The study will assess the applicability of GAIA definition for health outcomes. The health outcomes were selected based on relevance and perceived complexity of data collection. For future vaccine safety

study, sites should be able to link vaccination status information of pregnant women to obstetric and neonatal outcomes. Hence the project will also assess the current sites' capacity for data identification and collection on maternal immunisation status.

### 3 Objectives

The goals of this study are to estimate the minimum detectable risk of selected neonatal outcomes and to assess the applicability of GAIA case definitions in LMICs.

The GAIA definitions of interest for this study are: congenital microcephaly, low birth weight, neonatal death, neonatal infection, preterm birth, small for gestational age, stillbirth, and maternal immunisation.

#### 3.1 Primary objectives

1. To calculate the minimum detectable risk for each health outcome
2. To assess the applicability of the GAIA definitions for the health outcomes of interest and maternal immunisation.

#### 3.2 Secondary objectives

1. To assess the proportion of cases or exposures identified than can be classified according to each GAIA definition *level* of diagnostic certainty.
2. To identify factors that influence the applicability of the GAIA definitions.

#### 3.3 Exploratory objectives

1. To assess which missing data elements are preventing identified cases from meeting the GAIA case definition lowest level of diagnostic certainty.
2. To assess which missing data elements are preventing classified cases from meeting a better level of diagnostic certainty.

## 4 Methodology

### 4.1 Study design

This will be a prospective observational study at selected sentinel sites, mostly in LMICs.

As this study is observational, no changes to routine clinical and diagnostic practice will take place, however data recording from routine clinical practice is expected to be more complete and data access easier than in a retrospective study. During a feasibility assessment it was found that, at the majority of sites, medical records are not available in electronic format and archives are not easily accessible. Sites also expressed concerns on the limitation of their medical records maintenance: data that had been generated might not be recorded or might not be retrieved. Hence a prospective study design is proposed to ease access to quality data.

### 4.2 Study setting

The study will be performed at 25 sites in seven LMICs (Ghana, South Africa, Tanzania, Zimbabwe, Iran, India, Nepal) and one high-income country (HIC) (Spain). The sites consist of one primary care centre, four secondary and eighteen tertiary hospitals with a maternity ward. Sites have been selected based on site selection criteria and acceptable performance in a simulation exercise that tested sites' actual minimum capacity in data collection (Annex 1).

The following sites will participate (country, city, site). Sites characteristics are further described in Annex 2:

### 4.3 Study population

The study population will consist of all infants delivered (including stillborn) at the site during a one-year period after study start and their mother.

Mothers of all infants (including prenatally and stillborn) with a diagnosis of at least one condition of interest during the study period delivered at the site may be invited to participate in the study.

Since some sites may exceed the required number of infants with the outcome (as per section 5.1), 100 cases for each outcome will be consecutively recruited.

#### *Inclusion criteria*

The inclusion criteria for infants (alive or stillborn) are listed below. Mothers of eligible infants will also be enrolled.

- Delivered at the site at which the study takes place
- With a diagnosis of one of the health outcomes of interest at the same site during the study period
- Informed consent from mother

#### *Exclusion criteria*

- Infants not delivered at the site; including children diagnosed with one of the outcomes of interest at the site during the study period but not delivered at the site
- Spontaneous abortions (i.e. pregnancy loss prior to the prespecified gestational age that defines a stillbirth)
- No informed consent given

#### 4.4 Study period

Infants (including stillborn) delivered over a one-year period (tentatively between February 1, 2019 and January 31st, 2020) with one of the outcomes of interest will be eligible for inclusion. Data collection on identified cases will continue for an additional 28 days, covering the neonatal period for the last delivery registered.

#### 4.5 GAIA definitions

GAIA case definitions for the following health outcomes will be used (Annex 3):

- Congenital microcephaly [13]
- Low birth weight [14]
- Neonatal death [15]
- Neonatal infection [16]
- Preterm birth [15]
- Small for gestational age [17]
- Stillbirth [18]

The GAIA definition for maternal immunization [15] will be used to assess exposure to maternal tetanus vaccination or any other vaccine provided during pregnancy.

#### 4.6 Registration of all deliveries

All deliveries that take place at the site within one year of study start will be registered. This will include the date of delivery, the delivery outcome (live birth, foetal death), the sex, birth weight, gestational age, head circumference and the presence of any of the conditions of interest within 28 days of birth.

#### 4.7 Case identification and vaccine exposure assessment

Identified cases are defined as children delivered at the site with a diagnosis of one of the health outcomes of interest at the same site. A list of potential cases will be drawn on a regular basis (e.g. weekly) from relevant data sources (see section 3.7).

#### 4.7.1 Identification of congenital microcephaly

Congenital microcephaly is defined by the measurement of occipital-frontal circumference (head circumference) that is more than 2 standard deviations below the mean for age and sex or less than the 3rd percentile for age and sex [13]. Congenital microcephaly can be diagnosed *prenatally* ( $\geq 24$  weeks of gestational age) or *postnatally* (measurements up to 6 weeks after birth). For this study, we will only consider postnatally diagnosed microcephaly.

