## 4.9 Data collection

Each delivery that takes place at the site will be registered and the occurrence of any outcomes of interest within 28 days of birth will be recorded in the electronic data capture system (EDC). In addition, the sex, birth weight, gestational age and the head circumference will be collected. From this, the total number of live births over one year and the total number of cases identified among those delivered at the site will be derived.

Once an outcome occurs and the inclusion and exclusion criteria are met (including informed consent), the infant enters the study. At each site, cases with outcomes of interest will be consecutively recruited into the study, until 100 cases for each outcome have been recruited, or the end of the study period is reached, whichever occurs first.

One infant may present with more than one outcome under study; cases will be recruited for all outcomes until 100 cases for each outcome has been reached. . Data on case ascertainment for each case and maternal vaccination status of the case's mother will be collected in an electronic CRF in an electronic data capture (EDC) system. CRFs are available in Annex 5. If necessary, a paper CRF may be used as an intermediary step.

The EDC system will generate a unique ID for each child. Forms for child and mother shall be automatically linked to this unique ID where appropriate. Country and site codes shall also be assigned by the data management centre.

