#### Level 3B of diagnostic certainty

1. Live birth, stillbirth, or spontaneous or therapeutic abortion  
AND
2. Case meets criteria for microcephaly using a validated algorithm: 1 inpatient diagnosis OR 2 outpatient diagnoses OR 1 outpatient diagnosis AND death in first year using the following diagnostic codes ICD-9-CM code 742.1 or ICD-10-CM code Q02

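### Congenital microcephaly is defined by measurements up to 6 weeks after birth, but the register that supplies the case count records outcomes only to day 28

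*Protocol*

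**What the plan says.** Section 4.7.1 allows a postnatal diagnosis of microcephaly to rest on "measurements up to 6 weeks after birth" and adds: "For this study, we will only consider postnatally diagnosed microcephaly". In Annex III, Levels 2A, 2B and 3A accept a measurement up to 6 weeks, and the timing question of the microcephaly CRF (Annex V, Part 2, question 4) has an answer category that runs to 6 weeks. One of the three Level 3B routes is "1 outpatient diagnosis AND death in first year", and CRF item 5d asks for it.

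The recording rules are shorter. The delivery register notes "the presence of any of the conditions of interest within 28 days of birth" (section 4.6). In the EDC, "the occurrence of any outcomes of interest within 28 days of birth will be recorded" (section 4.9), and the same section derives each site's total number of identified cases from that record. Section 4.4 closes the study as follows: "Data collection on identified cases will continue for an additional 28 days, covering the neonatal period for the last delivery registered".

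The inclusion criterion in section 4.3 does not mention 28 days. It asks for an infant "With a diagnosis of one of the health outcomes of interest at the same site during the study period".

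**The concern.** A 28-day window suits neonatal death and neonatal infection, which are defined within 28 days. Low birth weight, preterm birth, small for gestational age and stillbirth are settled at birth. Microcephaly is the only one of the seven outcomes whose defining window runs past day 28.

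An infant first measured on day 35 satisfies section 4.7.1 and the inclusion criteria, and fits a CRF answer category, but has no place in the register. Sites can reasonably differ on whether to enrol such an infant. The infant could then count in the applicability analysis (section 5.2.2, which uses cases with a completed CRF) while missing from the case total and from the site-identified rates in section 5.2.1.1. The limitations in section 6 mention care not sought or sought elsewhere in the first month, but not this mismatch.

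**Working it through.** The protocol gives no figure to reproduce here; the check compares time windows.

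**Per-infant window.** The definition runs to 6 × 7 = 42 days (4.7.1) and recording to 28 days (4.6, 4.9). The gap is 42 − 28 = 14 days, and 14/42 = 33% of the measurement window. For the CRF category running from 36 h to 6 weeks, the unrecorded part is 14 × 24 / (42 × 24 − 36) = 336/972 = 34.6%. These are shares of time, not of cases.

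**Calendar end.** With the tentative last delivery on 31 January 2020 (4.4), collection ends 28 days later, on 28 February 2020. A birth on 17 January reaches day 42 on that date; births from 18 to 31 January do not. That is 14 of 365 birth days, or 3.8%. The 14 days follow from the 28-day rule whatever the actual dates are; section 10 gives a different calendar (May 2019 to August 2020), which does not alter the rule.

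**Levels of certainty against day 28 (Annex III).**

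| Level | Timing or route | Reachable by day 28? |
|---|---|---|
| 1 | measured at 24 to 36 h | yes |
| 2A, 2B | first 24 h, or after 36 h up to 6 weeks | yes; days 29 to 42 unrecorded |
| 3A | any time up to 6 weeks | yes; days 29 to 42 unrecorded |
| 3B | one inpatient code, or two outpatient codes, or one outpatient code plus first-year death | yes; later second codes and deaths unseen |
| 4 | inspection, or a code that fails the 3B algorithm | yes |

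None of the six levels is out of reach. For the death route, 365 − 28 = 337 of 365 days (92%) lie beyond day 28, again as a share of time. An infant moves from 3B to 4 only if all of these hold: no usable head circumference, no inpatient code, exactly one outpatient code by day 28, and a second code or death after day 28.

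**Possible size.** The protocol does not say what share f of cases is first measured on days 29 to 42. As an assumption, take f = 0%, 5%, 10% and 33%. The register count is then short by the same percentage. If those infants were also not enrolled, and 100 cases would otherwise have been available, the 95% half-width at a proportion of 50% is 1.96 × √(0.25/n):

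| f | n | half-width (percentage points) |
|---|---|---|
| 0% | 100 | 9.8 |
| 5% | 95 | 10.1 |
| 10% | 90 | 10.3 |
| 33% | 66.7 | 12.0 |

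Precision changes little for small f. The main effect is on what the count and rate mean.

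**The case against.** The strongest reply is that measurement is centred on birth. Sections 4.6 and 4.9 list head circumference beside sex, birth weight and gestational age, and the back-end rate in section 5.2.1.1 uses that value. Cases are sought mainly in maternity wards, pediatric wards and neonatal intensive care, where one inpatient code already meets Level 3B. Section 4.4 sets a calendar end, not a per-infant cut-off, so an infant diagnosed on day 35 can be enrolled. Section 6 already warns that rates may be too low.

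Most of this stands, and it limits the size. It does not remove the conflict, because the case total comes from the 28-day record. Section 5.2.1.1 also restricts the back-end microcephaly rate to sites that routinely collect head circumference, so the protocol expects some that do not; a later first measurement is more plausible there.

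A reader might infer three stronger things that the protocol does not support:

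- That whole levels of certainty cannot be captured. The table above shows otherwise.
- That about a third of cases are lost. The 33% is a share of days, and no case figure is given.
- That the first-year-death route cannot be assessed at all. A death inside the collection window is observed. Nor does anything in the protocol show that two outpatient codes by day 28 are rare.

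**Conclusion.** The point holds as a mismatch of windows. Microcephaly is defined to 42 days, eligibility has no day limit, and the count is taken to day 28, so the numerator does not match its own definition. Whether a late-measured infant is enrolled is left to each site's reading, and infants born in about the last 14 days cannot complete the definition's window under any reading. The undercount could be zero if every site measures at birth, and its size cannot be derived from the protocol. Regrading from Level 3B to Level 4 is confined to the narrow group described above. This is a minor point that is cheap to settle. Any effect on the count comes from the data window and should not be read as a lack of site capacity, which is what the study sets out to assess.

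**What to change.** Use one window for microcephaly in sections 4.4, 4.6, 4.7.1 and 4.9 and in the CRF timing item. Either option will do:

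1. Extend record review for this outcome alone to day 42. The cost is 14 more days of record review; on the tentative dates it would end on 13 March 2020 instead of 28 February 2020.
2. Count only measurements and diagnoses to day 28, in both register and CRF, and label the result a 28-day rate. The cost is wording plus one CRF change: the timing item, as shown in Annex V, has a single category from 36 h to 6 weeks and no measurement date, so it must be split at day 28 or a date added. Cases first measured later are given up openly.

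In either case, state in section 6 that the Level 3B route of one outpatient diagnosis plus first-year death is observed only for deaths within the data-collection window.
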